#### Unique Interventions

Many of the interventions selected to be offered as a part of the MP3 Youth protocol have been well documented in the literature and outlined in other papers [7,50,51]. This paper does not describe the rationale or process for HIV testing, linkage to care, family planning (condoms and contraception), or male circumcision—these processes are well known and documented—but discusses PrEP and CCT, two of the unique intervention components included in the MP3 Youth pilot study combination package. We outline our specific procedures for implementing these interventions as part of the innovation of the MP3 Youth protocol.

##### Pre Exposure Prophylaxis

For PrEP, Truvada or tenofovir disoproxil fumarate/emtricitabine (TDF/FTC) will be offered to out-of-school females aged 18 to 24 years as part of a demonstration project within this pilot study. Given that HIV prevalence for women in Kenya peaks earlier than men [11], we believe it is reasonable to provide PrEP only to eligible females aged 18 to 24 years. Our MP3 Youth mathematical modeling confirmed the additive role of PrEP as a prevention intervention component for women when offered during the highest window of HIV risk (from ages 18 to 24). The National AIDS and STI Control Program (NASCOP) in Kenya will offer PrEP as part of their prevention services as PrEP was officially approved for use in Kenya [52]. The US President’s Emergency Plan for AIDS Relief (PEPFAR) program in Kenya has also included PrEP as an intervention for the HIV prevention initiative called DREAMS [53]. This protocol will assess potential feasibility and implementation issues of offering PrEP to adolescent females in Kenya.

We will measure adherence to TDF/FTC for PrEP by employing pharmacological and non-pharmacological measures of adherence. Measures include self-report, electronic medication vials (eCAPs), and analysis of tenofovir diphosphate (TFV-DP) and emtricitabine triphosphate (FTC-TP) drug levels as assayed from dried blood spots (DBS). eCAPs record the time and date when each pill bottle is opened. This technology was successfully used in other studies [54,55]. DBS will provide biomarker data for participant adherence to TDF/FTC for PrEP. DBS is relatively easy to collect, store (within time constraints), and transport [56-58], making it an appropriate method for mobile health events.

##### Conditional Cash Transfers

CCTs will be offered to girls enrolled in school (aged 15 to 24 years) and their families as part of the MP3 Youth package. The girls will be required to attend school at least 80% of the time in order for her and her family to receive the CCT. This will be measured by visiting the schools to check attendance. Much of the CCT evidence base has come from government sponsored programs, like the Mexico Opportunidades program designed as an anti-poverty program with positive impacts on social, economic, and health indicators [59]. CCT programs have demonstrated multiple impacts, such as keeping girls in school and measurable health benefits. The National Government of Kenya, in collaboration with the United Nations Children's Fund (UNICEF) and the World Bank, initiated a program in 2002 called the “Kenya *Cash Transfer Program* for Orphans and *Vulnerable Children.”* The program transferred USD $14 to $28 per month (depending on the number of vulnerable children in the household) to vulnerable youth in Kenya [60]. A recent study by Handa and colleagues (2014) evaluated the Kenya cash transfer program and found a 31% reduction in sexual debut [61]. The MP3 Youth pilot study protocol will offer critical information on the feasibility of keeping girls in school using CCT as an intervention.

#### Cohort Follow-Up Schedules

Participants who attend the mobile MP3 Youth events will be enrolled into 4 cohorts which will be followed up for a period of 12 months via unstructured supplementary service data (USSD) and SMS text message (short message service, SMS) surveys and/or in-person computer-assisted personal interview (CAPI) surveys. The PrEP cohort will be followed up monthly for the first 6 months and every 3 months for the remaining 6 months in a mixture of in-person clinical visits and SMS and USSD surveys to facilitate adherence and conduct laboratory assessments (for HIV and pregnancy). The CCT cohort will be followed up every 3 months (0, 3, 6,9,12 months) for 12 months using an in-person CAPI and school registers checked for attendance. The HIV-positive cohort will also be followed up at intervals of 3 months via SMS and USSD surveys. A random subset of the HIV-negative youth who agree to be called in one year will receive a phone call to assess their HIV retesting behaviors and intentions. The HIV-positive cohort will undergo a clinical assessment at baseline and at month 12 (CD4 and viral load). The CCT cohort will undergo a clinical assessment at baseline and at month 12 (HIV testing and counseling and pregnancy testing). We will administer SMS and/or USSD and CAPI surveys to the cohorts to assess longitudinal self-reported behaviors. During all clinical/laboratory assessments, adverse events will be assessed.

#### Biomarkers and Adherence

Although efficacy of the individual components of the intervention package was already demonstrated in well-conducted randomized trials, we are electing to re-do CD4 and viral load levels (biomarker proxy for adherence) at 12 months in the HIV-positive cohort and collect biomarker data from the PrEP cohort to monitor adverse events and, in case of seroconversion, resistance. eCAPs and DBS will be used to monitor adherence to TDF/FTC. This combination of self-report and biomarker data will be sufficient to determine the feasibility of implementing the package of interventions and tracking youth sexual behaviors prospectively.

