#### Participants and Sample Size

In the cross-sectional portion of the study, we plan to enroll approximately 1000 youth (ages 15 to 24) over the course of 10 mobile events, held for 7 to 10 days each. We plan on enrolling a sub-section of the enrolled participants into longitudinal cohorts (approximately 300 youth).

The pilot study is not meant to provide a definitive test of the combination package efficacy. Nevertheless, power calculations can provide an idea of the magnitude of temporal effects on ART adherence or school attendance that could be reliably detected using conventional tests of significance. Assuming at least an 80% retention rate at the 12-month follow-up, a minimum of 40 CCT cohort participants, 40 PrEP cohort participants, and 80 HIV-positive cohort participants will contribute data for all planned assessments. A paired-samples *t* test with 80 pairs can detect a difference in means of one-third of a standard deviation (*d*=.33) with 83% power. A paired-sample *t* test with 40 pairs can detect a difference in means of *d*=.45, 80% power.

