### Target Sample Size

As stated previously, the MP3 Youth package will be offered to approximately 1000 youth who attend the mobile events. These participants will be part of the cross-sectional analyses. In addition, a subset of youth will be enrolled in longitudinal cohorts. The cohorts and their corresponding sample sizes are shown in Textbox 3.

Cohorts and sample sizes.CohortsHIV-positive cohort:All participants who test HIV positive (including participants who report being positive at baseline and are retested) during all mobile events will be invited to enroll in the longitudinal cohort using SMS/USSD surveys to collect data.Participants will be given mobile phones.The target HIV-positive sample size is approximately 100.Conditional cash transfer (CCT) cohort:In-school girls between 15 to 24 years of age who test HIV negative will be screened for eligibility at each of the mobile events.The target CCT sample size is approximately 50.Pre-exposure prophylaxis (PrEP) cohort:Out-of-school girls who test HIV negative and are between 18 and 24 years of age will be screened for eligibility at each of the mobile events.Participants will be given mobile phones.The target PrEP sample size is approximately 50.HIV-negative cohort:A random selection of participants who test HIV negative at the mobile events will be asked to complete one follow-up phone call at 12 months to assess willingness and intention to undergo HIV retesting (no study phone will be provided).The target sample size is approximately 100.

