### Study Outcomes

Study outcomes were developed by an expert panel during the formative phases of protocol development to evaluate the objectives of the study and the aforementioned methods employed to deliver the interventions (see Multimedia Appendix 1). The primary and secondary outcomes of MP3 Youth are shown in Textbox 4.

Primary and secondary outcomes of the MP3 Youth protocol.OutcomesPrimary study outcomes (cross-sectional and cohort)Intervention uptake (acceptability) and coverage (feasibility)CoverageThe proportion of youth in the community who attend each mobile event (estimated from youth population denominator)EnrollmentThe number of participants who consent to being enrolled in the study during each mobile event.UptakeThe proportion of eligible participants who choose one or more components of their tailored combination package (including combinations of interventions components)Intervention acceptabilitySatisfaction with mobile event services (computer-assisted personal interview at exit from mobile event)Secondary study outcomesAdherence to medication (HIV-positive and pre-exposure prophylaxis cohort participants only)Adherence to once daily Truvada (pre-exposure prophylaxis, PrEP) among HIV-uninfected eligible females and patterns of adherence and sexual HIV acquisition risk exposure (PrEP cohort participants only).Measured by self-report, electronic medication vial, and clinical assessments: monthly for the first 6 months and every 3 months thereafter and dried blood spot for analysis of tenofovir disoproxil fumarate/emtricitabine and tenofovir diphosphate and emtricitabine triphosphate at month 2 and 9.Adherence to antiretroviral therapy (ART) (HIV-positive cohort participants only)Measured by quarter annual text messages/unstructured supplementary service data self-report at 0, 3, 6, 9, and 12 months.Point of care cluster of differentiation 4 (CD4) and baseline viral load by dried blood spot or plasma will be measured at mobile event baseline and repeated at 12 months.Feasibility of administering conditional cash transfer to keep girls in school over 12 months.Measured by school attendance (self-report and random checks for school attendance verification).

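### The 80 pairs for ART adherence discount only attrition, although participants not on ART at enrolment have no baseline adherence; the CD4 and viral-load proxy mixes the same two groups

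*Protocol article*

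**What the plan says.** **Who is in the cohort.** Target Sample Size (Textbox 3) invites "All participants who test HIV positive (including participants who report being positive at baseline and are retested) during all mobile events", and adds: "The target HIV-positive sample size is approximately 100". Youth diagnosed at the event and youth who already knew their status are therefore in one cohort. No ART-status criterion or subgroup is stated.

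**What is measured.** Study Outcomes (Textbox 4) lists ART adherence for this cohort by "self-report at 0, 3, 6, 9, and 12 months". CD4 is also listed there, and "baseline viral load by dried blood spot or plasma will be measured at mobile event baseline and repeated at 12 months". Biomarkers and Adherence gives the role of these markers: "we are electing to re-do CD4 and viral load levels (biomarker proxy for adherence) at 12 months in the HIV-positive cohort".

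**What is powered.** Participants and Sample Size offers its power calculations as a guide to the "magnitude of temporal effects on ART adherence or school attendance that could be reliably detected". "Assuming at least an 80% retention rate at the 12-month follow-up", it counts at least 80 HIV-positive participants with data at every planned assessment. It then gives 83% power for a paired t test with 80 pairs at d=.33.

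**What is analysed.** The Results section plans to show levels of and changes in adherence graphically. It refers to Multimedia Appendix 2, which is not shown, for the detailed analysis plan.

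**The concern.** Adherence to ART is defined only for someone who has been prescribed it. A participant diagnosed at the mobile event is linked to care from that event, so treatment can only follow enrolment. The month-0 adherence item has no value for that person, and no baseline-to-follow-up adherence pair can be formed. The stated count of 80 removes people lost to follow-up but not people with nothing to adhere to at baseline.

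The biomarkers raise a related difficulty. Between month 0 and month 12, viral load in an untreated participant who then starts ART moves because treatment began as well as because it was taken. A participant already suppressed at baseline has no room to improve. A change taken over the whole cohort would depend on the mix of the two groups.

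At stake are the pilot's stated precision for ART-adherence change and the reading of the biomarker data under the first secondary objective.

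**Working it through.** **Step 1: reproduce the plan's figures.** Target 100 × 0.80 retention = 80 participants, as stated. Power of a paired t test comes from the noncentral t distribution with n − 1 degrees of freedom and noncentrality d × √n. The article gives no significance level; two-sided 5% is assumed here. For n = 80 and d = 0.33 the noncentrality is 0.33 × 8.944 = 2.95 and power is 83.0%, matching the stated 83%. A one-sided test would give about 90%, so two-sided 5% is the reading that fits. The arithmetic is right.

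**Step 2: what 80 pairs requires.** Let p be the share of the 80 retained participants who are on ART at enrolment. Baseline-anchored adherence pairs number 80 × p, which equals 80 only if p = 1. The cohort definition explicitly includes both newly and previously diagnosed youth, and nothing in the article makes p equal to 1.

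**Step 3: size over a range of p.** The article does not give p, so the values below are assumptions.

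| p (assumed) | Pairs = 80 × p | Noncentrality at d = 0.33 | Power at d = 0.33 | d detectable with 83% power |
|---|---|---|---|---|
| 100% | 80 | 2.95 | 83% | 0.33 |
| 75% | 60 | 2.56 | 71% | 0.38 |
| 50% | 40 | 2.09 | 53% | 0.47 |
| 25% | 20 | 1.48 | 29% | 0.69 |

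**Step 4: the biomarker proxy.** Let g be the share newly diagnosed and s the proportion of them suppressed at month 12. Assume that none of them is suppressed at baseline and that the already-treated group stays constant at 70% suppressed. The whole-cohort change is then g × s, with no change among those already treated.

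- g = 50%: baseline is 0.5 × 70% = 35%. With s from 50% to 90%, month 12 is 60% to 80%, a gain of 25 to 45 points.
- g = 25%, s = 50%: gain 12.5 points.
- g = 75%, s = 90%: gain 67.5 points.

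All of g, s and the 70% are illustrative. They show that the change follows the case mix, and they do not predict what this study would find.

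**The case against.** The strongest reply is that the article does not specify the analysis being criticised. Adherence is to be shown with box plots and trajectory plots. The contrasts named in the Results section (baseline vs 6 months, 6 vs 12 months) are for risk behaviors. Denominators and stratification by ART status belong in the appendix that is not shown. The pilot also says that it is not a definitive test and that its power figures are only indicative.

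Much of this stands, and it rules out several stronger readings that a reader might infer:

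- *That 80 pairs cannot exist.* The share on ART is unknown. Pairs of later visits, such as month 6 vs month 12, remain possible for those on ART by the first of them. CD4 and viral-load pairs can exist for all 80.
- *That starting ART will be reported as improved adherence.* No pooled test of adherence change is specified, and nothing says that untreated participants are scored zero at month 0. The biomarker sentence is also compatible with reading a month-12 level.
- *That the first secondary objective goes unanswered.* Study Objectives words it as adherence to HIV care including ART. Linkage and initiation fall within that, and self-report after baseline still gives adherence levels among those treated.
- *That viral-load change mixes specimen types.* Textbox 4 permits either specimen but does not say that a participant changes type between visits.

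The reply does not reach two things that the article itself states. The count of 80 with data at all planned assessments deducts attrition only. The proxy label covers the whole HIV-positive cohort. An appendix could stratify the analysis, but the pair count and label printed here would still need correcting.

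**Conclusion.** The point holds as a correction to a stated count and a stated label. The 83% is right for 80 pairs, but 80 baseline-anchored ART-adherence pairs require every retained participant to be on ART at enrolment, which the cohort definition does not support. For assumed shares on ART of 75% down to 25%, pairs fall to between 60 and 20, and power at d=.33 to between about 71% and 29%. No single value in that range is a property of this protocol, because the share is not given.

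A month-0 to month-12 change in CD4 or viral load over the whole cohort can reflect starting ART rather than adherence. Calling it a proxy for adherence is sound only for those on ART. Whether the change will in fact be read that way cannot be settled from the article.

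**What to change.** 1. Record ART status at enrolment, with start date, if the baseline survey does not already do so.
2. Define change in ART adherence only among participants on ART at both compared assessments, for example month 6 vs month 12.
3. Report ART initiation as its own outcome, and month-12 viral suppression by ART status at enrolment.
4. Limit the description of CD4 and viral load as an adherence proxy to participants on ART.
5. In Participants and Sample Size, replace the single count of 80 adherence pairs with a range over plausible shares on ART, giving the power or detectable effect for each.

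The cost is wording and at most one baseline item. The downside is fewer pairs for the adherence-change analysis and a less favourable stated power. No visit or treatment procedure needs to change.

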### Study Population

The eligibility criteria for MP3 Youth are shown in Textbox 2.

General eligibility requirements for the pilot study.CriteriaInclusion criteriaAny male or female between the ages of 15 to 24 years.Able to understand spoken English, Kiswahili, or Dholuo.Willing to give informed consent (including emancipated minors), or, if younger than 18 years of age, has a parent or guardian willing to provide consent in addition to the minor’s assent.Willing to be tested for HIV.Willing to get a participant identification (ID) based on biometric finger scanning.Exclusion criteriaAny male or female younger than 15 years or older than 24 years of age.Unable to understand spoken English, Kiswahili, or Dholuo.If under 18 years of age, not an emancipated minor, and unable to get parental consent.

### Target Sample Size

As stated previously, the MP3 Youth package will be offered to approximately 1000 youth who attend the mobile events. These participants will be part of the cross-sectional analyses. In addition, a subset of youth will be enrolled in longitudinal cohorts. The cohorts and their corresponding sample sizes are shown in Textbox 3.

Cohorts and sample sizes.CohortsHIV-positive cohort:All participants who test HIV positive (including participants who report being positive at baseline and are retested) during all mobile events will be invited to enroll in the longitudinal cohort using SMS/USSD surveys to collect data.Participants will be given mobile phones.The target HIV-positive sample size is approximately 100.Conditional cash transfer (CCT) cohort:In-school girls between 15 to 24 years of age who test HIV negative will be screened for eligibility at each of the mobile events.The target CCT sample size is approximately 50.Pre-exposure prophylaxis (PrEP) cohort:Out-of-school girls who test HIV negative and are between 18 and 24 years of age will be screened for eligibility at each of the mobile events.Participants will be given mobile phones.The target PrEP sample size is approximately 50.HIV-negative cohort:A random selection of participants who test HIV negative at the mobile events will be asked to complete one follow-up phone call at 12 months to assess willingness and intention to undergo HIV retesting (no study phone will be provided).The target sample size is approximately 100.

### Study Outcomes

Study outcomes were developed by an expert panel during the formative phases of protocol development to evaluate the objectives of the study and the aforementioned methods employed to deliver the interventions (see Multimedia Appendix 1). The primary and secondary outcomes of MP3 Youth are shown in Textbox 4.

Primary and secondary outcomes of the MP3 Youth protocol.OutcomesPrimary study outcomes (cross-sectional and cohort)Intervention uptake (acceptability) and coverage (feasibility)CoverageThe proportion of youth in the community who attend each mobile event (estimated from youth population denominator)EnrollmentThe number of participants who consent to being enrolled in the study during each mobile event.UptakeThe proportion of eligible participants who choose one or more components of their tailored combination package (including combinations of interventions components)Intervention acceptabilitySatisfaction with mobile event services (computer-assisted personal interview at exit from mobile event)Secondary study outcomesAdherence to medication (HIV-positive and pre-exposure prophylaxis cohort participants only)Adherence to once daily Truvada (pre-exposure prophylaxis, PrEP) among HIV-uninfected eligible females and patterns of adherence and sexual HIV acquisition risk exposure (PrEP cohort participants only).Measured by self-report, electronic medication vial, and clinical assessments: monthly for the first 6 months and every 3 months thereafter and dried blood spot for analysis of tenofovir disoproxil fumarate/emtricitabine and tenofovir diphosphate and emtricitabine triphosphate at month 2 and 9.Adherence to antiretroviral therapy (ART) (HIV-positive cohort participants only)Measured by quarter annual text messages/unstructured supplementary service data self-report at 0, 3, 6, 9, and 12 months.Point of care cluster of differentiation 4 (CD4) and baseline viral load by dried blood spot or plasma will be measured at mobile event baseline and repeated at 12 months.Feasibility of administering conditional cash transfer to keep girls in school over 12 months.Measured by school attendance (self-report and random checks for school attendance verification).

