**Results:**

The combination HIV prevention package in this protocol includes (1) offering HIV testing and counseling for all youth; (2) voluntary medical circumcision and condoms for males; (3) pre-exposure prophylaxis (PrEP), conditional cash transfer (CCT), and contraceptives for females; and (4) referrals for HIV care among those identified as HIV-positive. The combination package platform selected is mobile health teams in an integrated services delivery model. A cross-sectional analysis will be conducted to determine the uptake of the interventions. To determine long-term impact, the protocol outlines enrolling selected participants in mutually exclusive longitudinal cohorts (HIV-positive, PrEP, CCT, and HIV-negative) followed by using mobile phone text messages (short message service, SMS) and in-person surveys to prospectively assess prevention method uptake, adherence, and risk compensation behaviors. Cross-sectional and sub-cohort analyses will be conducted to determine intervention packages uptake.

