### Aim 3: Pilot Study

The previous aims were completed to inform Aim 3 of this protocol. This section provides an overview of setting, participants, and details of how interventions can be implemented and how data should be collected. Our preliminary research confirmed that there were numerous examples of individual HIV prevention interventions aimed at addressing the drivers of the HIV epidemic among youth [18-30]. Many of the vertically-focused single interventions were efficacious, but there remained a need for combination approaches [8]. The studies reviewed as part of the systematic review informed our decision about the most effective and feasible components to include in the protocol for the combination package. These components are HIV testing and counseling (HTC) [31,32], condoms [33,34], family planning (contraception) [35,36], voluntary medical male circumcision [37-39], conditional cash transfers (CCTs) [40-44], pre-exposure prophylaxis (PrEP) [40,45,46], and HIV care and treatment [47,48]. All interventions included in the protocol to be offered as part of MP3 Youth were chosen because they were efficacious, youth-friendly, possible to implement in a mobile health setting, and potentially sustainable following the MP3 Youth study.

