#### MP3 Youth Package

Based on results of the first two aims, the gender-specific MP3 Youth package was developed (Figure 5). The tailoring of interventions to specific individuals is referred to as the “MP3 Youth package of services.” For all participating youth, the package will include HIV counseling and testing. For all HIV-positive participants, the package will include point of care cluster of differentiation 4 (CD4) and viral load testing, and facilitated linkage to care (n is approximately 100), including prevention of mother-to-child transmission for pregnant females. For all participating males, the package will also include condoms and voluntary medical male circumcision, whereas for all participating females the package will also include contraception (both male and female condoms) and family planning. PrEP will be included for HIV-negative, out-of-school females while CCT will be included for HIV-negative, in-school females. The protocol aims for approximately 1000 youth to be enrolled in the pilot study and from these, sub-cohorts of youth (approximately 300) will be followed up prospectively for 12 months to document behaviors and adherence related to selected interventions. In addition, follow-up by phone to approximately 100 youth who are HIV negative at baseline will assess whether or not they were HIV retested over the last 12 months or if they are willing to be retested at the 12-month follow-up period.

The combination MP3 Youth package menu options will be delivered through community-based mobile health teams and all interventions will be offered on-site. PrEP and CCT cohort enrollment will also be initiated on site and followed-up prospectively off-site. Mobile health teams will be able to select the most appropriate location within a community to set up tents to deliver the MP3 Youth packages. Mobile health events increase accessibility to the interventions and reduces stigma by offering it in the context of a health event where other youth-friendly services are also being provided [32,49].

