#### Study Objectives

The objectives of the pilot study were developed based on the formative stages of the protocol development by an expert panel that recognized the gaps that this study could fill. The primary objective is to determine the feasibility and acceptability of a pilot combination HIV prevention package specific for female and male youth (MP3 Youth) in Homa Bay County, Nyanza Province, Kenya. This will be determined by examining uptake and coverage of the intervention package among youth. The secondary objectives are (1) to examine adherence to HIV care including antiretroviral therapy (ART) among HIV-positive males and females 15 to 24 years of age; (2) to evaluate the feasibility of offering PrEP to high HIV risk out-of-school females 18 to 24 years of age and to contribute data to the current question of how best to initiate and support ongoing adherence for females using PrEP; (3) to assess the feasibility of delivering CCT to keep girls in school over the 12 months; and (4) to evaluate school attendance over 12 months of CCT cohort participants. For the logic model, see Multimedia Appendix 1.

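### The any-component uptake proportion sits at about 100% by construction, because every participant has agreed at entry to HIV testing and testing counts as a component

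*Protocol article*

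**What the plan says.** Study Objectives makes feasibility and acceptability of the package the primary objective and adds: "This will be determined by examining uptake and coverage of the intervention package among youth". Textbox 4 (Study Outcomes) labels uptake as the acceptability measure and coverage as the feasibility measure. It defines uptake as the "proportion of eligible participants who choose one or more components of their tailored combination package", followed by a parenthesis, "including combinations of interventions components". Textbox 4 lists coverage, enrollment (a count per event) and exit-interview satisfaction as separate primary items.

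Two other sections decide what that definition yields:

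- MP3 Youth Package: "For all participating youth, the package will include HIV counseling and testing". The abstract's Results give "offering HIV testing and counseling for all youth" as the first item of the package, and Aim 3: Pilot Study names testing first in its list of components.
- Study Population (Textbox 2), inclusion criteria: "Willing to be tested for HIV".

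The article does not exclude HIV testing from the components that count toward uptake.

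**The concern.** A youth who is unwilling to be tested cannot be a participant, so is not in the uptake denominator. A youth who is in the denominator has agreed to testing, which is in the package and counts in the numerator. The proportion is therefore fixed near its maximum before any choice about condoms, circumcision, contraception, PrEP or cash transfer is observed.

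The pilot is meant to help establish acceptability before a larger evaluation (Implication of Pilot Study Results). A package from which participants took nothing beyond the test would score almost the same on this measure as one that most of them took up in full. A figure near 100%, reported under the label of acceptability, could be read as evidence about the whole package when it mainly reflects the entry rule.

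**Working it through.** The article states no target, threshold, precision or power for uptake, so there is no figure to reproduce. The check is logical, with arithmetic to show its size.

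**Inputs**

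- Numerator rule: at least one component; denominator: eligible participants (Textbox 4).
- Testing is in every package (MP3 Youth Package), and willingness to be tested is required for entry (Textbox 2).
- N is about 1000 (Participants and Sample Size).
- h = share of eligible participants who take the HIV test. Not given. Willingness is not a completed test, so values from 95% to 100% are assumed.
- q = share who take any other component. Not given; varied from 0 to 90%.

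**Step 1: bound.** Anyone who takes the test has at least one component, so P(at least one) ≥ h for every q, with no independence assumption. The whole possible range of the outcome is h to 100%.

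**Step 2: size, treating the two choices as independent.** P(at least one) = 1 − (1 − h)(1 − q).

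| h (assumed) | q = 0 | q = 30% | q = 50% | q = 90% | Shift, q from 0 to 90% |
|---|---|---|---|---|---|
| 100% | 100% | 100% | 100% | 100% | 0 points |
| 99% | 99.0% | 99.3% | 99.5% | 99.9% | 0.9 points |
| 98% | 98.0% | 98.6% | 99.0% | 99.8% | 1.8 points |
| 95% | 95.0% | 96.5% | 97.5% | 99.5% | 4.5 points |

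Example: h = 95%, q = 50% gives 1 − 0.05 × 0.50 = 97.5%. Without independence, Step 1 still limits the shift to 1 − h, which is 5 points at h = 95%.

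**Step 3: the same outcome without the entry-required test.** The proportion then equals q and can take any value from 0 to 100%. The MP3 Youth Package section gives males condoms and circumcision, and females contraception and family planning, so nobody is left with an empty package and the denominator stays at about 1000. The 95% half-width is 1.96 × √(q(1 − q)/1000):

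- q = 10% or 90%: 1.9 points
- q = 30% or 70%: 2.8 points
- q = 50%: 3.1 points

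These show what N of about 1000 could resolve. They are not a forecast of q.

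**The case against.** The strongest reply is that this proportion is one descriptive line in a wider assessment. Textbox 4 also has coverage, enrollment and satisfaction. The parenthesis on combinations brings into the uptake outcome a breakdown that can separate test-only participants from those who took more. Multimedia Appendix 2, which is not shown, may report uptake by component. All of this stands and limits the point to the any-component proportion. It does not change how that proportion is defined: the parenthesis adds description and leaves the at-least-one rule in place, with testing counted.

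Reading eligible as eligible for a given component does not help either, since every participant is eligible for testing. The entry criterion itself has a purpose, because HIV status determines the package and the cohort. The point does not ask for it to be dropped.

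A reader might infer three stronger things that the article does not support:

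- *That the primary outcome is met by design.* No uptake threshold, test or decision rule exists to be met, and Participants and Sample Size says the pilot is not a definitive test of efficacy.
- *That refusals of testing vanish from the data.* Coverage needs an attendance count per event and enrollment is a count per event, so enrolled over attended can be derived. That ratio mixes test refusal with refusal of consent, parental consent or biometric scanning, but the loss is visible.
- *That testing acceptance among attendees would be misreported by a known amount.* The article gives no refusal rate and does not list testing acceptance among attendees as an outcome. Any size put on this would be assumption.

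Data Collection already says that the exit interview is for youth who are eligible, consent and register, so nothing needs adding there.

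**Conclusion.** The point holds in a limited form. As Textbox 4 is worded, the any-component uptake proportion is at about 100% by construction and cannot discriminate between high and low acceptability of the rest of the package. For h between 95% and 100%, it moves by at most 5 points whatever the uptake of everything else, and by no more than 1 point when h is 99% or above. About 100% is the right description, and exactly 100% would not be, because willingness at entry is not a completed test. The values of h are assumptions; the lower bound of h is not.

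This is a stated rule with an uninformative result, so it is not merely detail left to an appendix. It does not undermine the primary objective as a whole: uptake by combination, coverage and exit satisfaction are unaffected by this ceiling.

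**What to change.** In Textbox 4:

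1. Define the composite uptake outcome as at least one component other than the HIV testing and counseling required for entry.
2. Report uptake also by component, each among the participants eligible for it.
3. Report enrollment also as a proportion of attendees, using the attendance count that coverage already needs, and note that this ratio mixes test refusal with refusal of consent or biometrics.

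The cost is wording. Service uptake is already tracked through the fingerprint identifier (Biometric Data Collection), so no new data are needed. The downside is that the reported uptake figure will be lower than the near-100% value the present definition would give.
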